## Abstract

**Background:**

Weight loss in overweight or obese breast cancer patients is associated with an improved prognosis for long term survival. However, it is not clear whether the macronutrient composition of the chosen weight loss dietary plan imparts further prognostic benefit. A study protocol is presented for a dietary intervention to investigate the effects of weight loss dietary patterns that vary markedly in fat and carbohydrate contents on biomarkers of exposure to metabolic processes that may promote tumorigenesis and that are predictive of long term survival. The study will also determine how much weight must be lost for biomarkers to change in a favorable direction.

**Methods/Design:**

Approximately 370 overweight or obese postmenopausal breast cancer survivors (body mass index: 25.0 to 34.9 kg/m^2^) will be accrued and assigned to one of two weight loss intervention programs or a non-intervention control group. The dietary intervention is implemented in a free living population to test the two extremes of popular weight loss dietary patterns: a high carbohydrate, low fat diet versus a low carbohydrate, high fat diet. The effects of these dietary patterns on biomarkers for glucose homeostasis, chronic inflammation, cellular oxidation, and steroid sex hormone metabolism will be measured. Participants will attend 3 screening and dietary education visits, and 7 monthly one-on-one dietary counseling and clinical data measurement visits in addition to 5 group visits in the intervention arms. Participants in the control arm will attend two clinical data measurement visits at baseline and 6 months. The primary outcome is high sensitivity C-reactive protein. Secondary outcomes include interleukin-6, tumor necrosis factor-α, insulin-like growth factor-1 (IGF), IGF binding protein-3, 8-isoprostane-F2-alpha, estrone, estradiol, progesterone, sex hormone binding globulin, adiponectin, and leptin.

**Discussion:**

While clinical data indicate that excess weight for height is associated with poor prognosis for long term survival, little attention is paid to weight control in the clinical management of breast cancer. This study will provide information that can be used to answer important patient questions about the effects of dietary pattern and magnitude of weight loss on long term survival following breast cancer treatment.

**Clinical Trial Registration:**

CA125243

## Background

Breast cancer is the most common form of cancer in women in the United States [1] and one of the top ten causes of death [2]. Recent estimates show age-adjusted incidence rate is 123.8 per 100,000 women per year [3]. Body fat is now established as being causally related to postmenopausal breast cancer [1,4-8], with overweight or obese women having almost twice the rates of cancer recurrence and up to 1.5 times the risk of death from breast cancer compared to women in the healthy weight range [1,4-7,9-16]. These are alarming findings since the majority of women in the United States are now overweight or obese (i.e. body weight (kg)/height (m^2^) > 24.9) [17]. This situation is compounded by the fact that weight gain is common post-diagnosis [18,19].

Studies have shown that losing body weight is protective against breast cancer [20,21], and that weight loss can be achieved through multiple approaches [22]. However, it is unclear whether different diets modeled on popular weight loss programs which vary markedly in macronutrient composition differentially affect long term survival following breast cancer treatment [23-35]. Cross sectional, case control and cohort data is conflicting on fat and carbohydrate intake and breast cancer risk [36-40], with little data available about dietary effects on breast cancer survival [41,42]. Moreover, it is not known whether improvement in biomarkers is progressive with increasing weight loss. This could result in very different clinical guidance related to weight loss in these women.

A number of candidate mechanisms including chronic inflammation [43-46], cellular oxidation [47-57], and insulin resistance [58] may explain the link between energy balance and long term survival following breast cancer treatment. Biomarkers that relate to these mechanisms can be measured in blood and urine to assess potential effects. Although maintaining a healthy body weight is protective against breast cancer and weight loss is feasible in post-menopausal breast cancer survivors [59,60], there are no published studies investigating how fat loss using different dietary macronutrient compositions (i.e. dietary patterns) influences these metabolic and hormonal processes. The CHOICE study seeks to address these questions in an effort to strengthen the evidence base on modifiable lifestyle factors, specifically weight loss, and their effects on long term survival following treatment for breast cancer. Typically, weight loss plateaus after 6-months and most weight is regained after 1 to 5 years [61-64], so in addition to determining whether dietary pattern matters, it will also become critical to identify ways to promote weight loss maintenance so that any protection gained is not transient.

## Methods/Design

### Study Design

The study, called CHOICE, is a non-randomized, controlled trial in post-menopausal breast cancer survivors investigating whether an energy restricted dietary pattern, i.e. low carbohydrate, high fat or low fat, high carbohydrate, with progressive fat loss during a weight loss program can alter the likelihood of long term survival following treatment for breast cancer as reflected in metabolic and hormonal prognostic biomarkers. A total of 370 women will be accrued and assigned to one of the two dietary intervention arms based on eating preferences or a non-intervention control arm (n = 135 to each intervention arm, n = 100 to the control arm) and followed for 6 months as illustrated in Figure 1. Anthropometric measurements are conducted and biomarkers collected at baseline and 6 months in the control arm, and monthly in the intervention arms in order to model the shape of the metabolic and hormonal response curves.

**Figure 1 F1:**
[figure not shown]
Project Overview

### Study Aims

#### Primary Aim

The primary aim of the study is to investigate whether dietary pattern (low carbohydrate or low fat) alters the patterns of change observed in circulating factors involved in chronic inflammation, glucose homeostasis, cellular oxidation, and steroid hormone metabolism during progressive loss of body fat. The primary outcome measure is high sensitivity C-reactive protein. All other measurements are considered secondary endpoints.

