### Data Analysis

All data elements collected will be examined using descriptive statistics (mean, median, SD, range, percentiles, proportion) and graphical summaries (box plots, profile plots by time and diet group). Log transformations will be made before further analysis to stabilize variances as needed.

The primary hypothesis on C-reactive protein will be tested using the following ANCOVA model:

Where Y_4 _is the outcome measure at the end of 6 months, Y_1 _is the outcome measure at baseline, and, GLYC is a 2-level indicator for dietary pattern. This method of analysis adjusts for any remaining pre-treatment differences between groups (a precaution against imbalance after diet assignment) and reduces variability in the data being analyzed [97], thus improving the power of the test for the main effect of interest, b_2_.

There will be a wealth of information in the repeated measures on each subject; the results for all measures using all available data from all time points will be estimated in a mixed-effects repeated measures model to assess the slopes and between group differences after each month of weight loss [98]. The power of this approach lies in its ability to incorporate all of the available longitudinal data even in the unbalanced case, that is, when some of the observations are missing for one or more individuals. Observations within a person over time are allowed to be correlated while observations across individuals are assumed to be independent. These models will also be used to explore the effects of breast cancer stage, BMI (a time-varying covariate) and age.

Depending on the appearance of change over time (seen in the profile plots of each outcome measure by time and diet) linear or nonlinear mixed models will be used. If the trend appears to be linear, the following model for the response vector ***y***_i _for the *i*th group will be used:(1)

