where **b**_*i *_~ *N *(0,D) and **e**_*i *_~ *N *(0,R_*i*_) are independent. X_*i *_is a fixed effects design matrix that includes indicators for diet group (1, 2), assessment time (after each 1.5 kg fat loss, and potential covariates (age) or confounders (disease stage, BMI). **Z**_*i *_is a design matrix for the random effects that allows random subject deviations from the population average response. The marginal distribution of **y**_*i *_is normal with mean **X**_*i *_*β *and variance . Parameter estimation in SAS allows a wide range of specifications for the forms of **D **and **R**, and combines empirical Bayes and restricted maximum likelihood using the EM algorithm.

If the descriptive graphs suggest a nonlinear model is appropriate, we will estimate:(2)

Where **b**_*i *_~ *N *(**0**,**D**) and **e**_*i *_~ *N *(**0**,**R**_*i*_). The marginal distribution of **y**_*i *_is difficult to find in most cases, but its mean and variance can be approximated by

Where  is the partial derivative of *f *(⋅) with respect to **b**_*i*_. Parameter estimation in SAS combines a linearization algorithm, such as Gauss-Newton, and the method of Laird-Ware for linear mixed models. We will explore the use of nonlinear models only if it appears that the response trajectory of *Y *over time could be fit well by a smooth nonlinear function. Otherwise, simpler piece-wise linear mixed models will be fit using Equation 1 above.

Secondary measures in the 4 families of outcomes will be assessed using the same statistical methods described above for the primary measures. That is, ANCOVA assessment of the measure by diet group at 6 months followed by an exploratory analysis with mixed models using all available data.

Mixed models will also be used to estimate the effects of fat loss on the 4 families of outcomes. Fat loss and weight loss will be modeled with the expectation that differences across diets will be minimal, and success in weight loss better explained by age, initial BMI, and usual level of physical activity.

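### The primary CRP test compares the diets at month 6 only, a narrower question than the primary aim of a difference in pattern of change

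*Protocol article*

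**What the plan says.** The Primary Aim of the protocol article asks whether dietary pattern "alters the patterns of change observed in circulating factors" while body fat is being lost, and adds: "The primary outcome measure is high sensitivity C-reactive protein". The Study Design section explains that measurements are monthly in the two diet arms "in order to model the shape of the metabolic and hormonal response curves". The Eligibility section gives seven fasting blood samples per intervention participant.

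The Data Analysis section then states: "The primary hypothesis on C-reactive protein will be tested using the following ANCOVA model". Its terms are a month-6 response (it "is the outcome measure at the end of 6 months"), a covariate that "is the outcome measure at baseline", and a two-level diet indicator. The control arm is therefore not in this test.

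The same section also plans a mixed-effects model for all measures at all time points, to estimate slopes and monthly diet differences. Whether it is linear, nonlinear or piecewise depends on how the profile plots by time and diet look. The secondary measures are to be analysed as the primary one is, and this is spelled out as an ANCOVA at 6 months "followed by an exploratory analysis with mixed models using all available data". The section expects 10% loss to follow-up, no more than about 5% of observations missing, data missing at random, and an intent-to-treat analysis.

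**The concern.** The aim, and the reason given for monthly sampling, concern the course of CRP over six months. The only analysis given the status of a hypothesis test concerns its level at the end. Two consequences follow.

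- If the diets take CRP along different paths that meet at month 6, the primary result will be null. With the aim worded as it is, that null would be read as no effect of diet on the pattern of change, which an end-point test cannot support.
- A woman without a month-6 sample has no response in the primary test, whatever she contributed earlier. That fits poorly with the intent-to-treat label and with the section's own argument that the mixed model can use incomplete series.

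The analysis that could answer the aim has its functional form settled only after the data have been plotted by diet, so it cannot serve as a confirmatory answer in its place.

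**Working it through.** **Sample count.** One baseline and six monthly samples make 7. The ANCOVA uses 2, so 5 are unused in that test.

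**Power.** The article states no alpha, SD, correlation or target difference, so there is no figure of the plan to reproduce. The following are assumptions: two-sided 5%, 135 women per diet arm (Study Design), CRP on a scale with SD 1 (for example after log transformation), and compound symmetry (CS) with correlation 0.5-0.7 or AR(1) with monthly correlation 0.8-0.95.

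Let V be the 6 x 6 covariance of months 1-6 given baseline, W = V x 2/135 the covariance of the six diet differences, and d the vector of true differences.

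- Month-6 ANCOVA: SE = sqrt(V66 x 2/135), with V66 = 1 - r^2 and r the correlation between baseline and month 6. Power is Phi(|d6|/SE - 1.96) plus a negligible second tail.
- 6-df joint monthly test: non-central chi-square with non-centrality d'W^-1 d.
- 1-df linear trend: generalised least-squares slope with x = (1,...,6)/6.

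Example, CS 0.5, d6 = 0.3: V66 = 1 - 0.25 = 0.75; SE = sqrt(0.75 x 2/135) = 0.105; 0.3/0.105 = 2.85; power = Phi(2.85 - 1.96) = 81%.

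Power (%) for linear divergence to 0.3 SD at month 6, and for a hump of 0.3 SD x (0.33, 0.67, 1, 0.67, 0.33, 0):

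| Correlation | V66 | Linear: ANCOVA | Linear: 6-df | Linear: trend | Hump: ANCOVA | Hump: 6-df | Hump: trend |
|---|---|---|---|---|---|---|---|
| CS 0.5 | 0.750 | 81 | 74 | 94 | 5 | 74 | 10 |
| CS 0.7 | 0.510 | 93 | 91 | 99 | 5 | 92 | 7 |
| AR(1) 0.8 | 0.931 | 72 | 45 | 73 | 5 | 67 | 7 |
| AR(1) 0.9 | 0.718 | 83 | 56 | 83 | 5 | 94 | 5 |
| AR(1) 0.95 | 0.460 | 95 | 79 | 95 | 5 | >99 | 5 |

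The ANCOVA has only its alpha level when the difference has closed by month 6, and real power when it has not. The joint test sees the hump but is weaker than the ANCOVA in every linear case. The trend test is never below the ANCOVA in the linear cases and is almost blind to the hump.

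**Women who miss month 6.** The intended 135 per arm and 10% loss give about 13.5 women per arm, or 27 in all. Suppose 10% miss month 6 but have months 1-5. Let R^2 be the share of the baseline-adjusted month-6 variance explained by months 1-5. The ANCOVA variance is proportional to 1/0.9, and the mixed-model month-6 contrast to (1 - R^2)/0.9 + R^2. The ratio is 1 - 0.1 R^2.

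- CS 0.5: the partial correlation is 0.25/0.75 = 1/3, so R^2 = 5(1/9)/(1 + 4/3) = 0.24, a reduction of 2.4%.
- AR(1) 0.95: R^2 = 1 - 0.0975/0.460 = 0.79, a reduction of 7.9%.

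The other three cases lie between (3.2%, 6.1%, 7.4%). If only 5% miss month 6, the ratio is 1 - 0.05 R^2 and the reduction is half as large. Women who leave before month 5 also yield less.

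**The case against.** The strongest defence is that a broad aim with one simple end-point test, supported by longitudinal modelling, is common and legitimate, and that an end-of-programme difference is a sensible primary question. That stands. It is why the primary hypothesis can be reworded and the end-point kept.

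Four stronger readings are tempting and are not supported.

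- A reader might infer that five of seven CRP samples are discarded. They are not: the Data Analysis section puts all measures at all time points into the mixed model. They are unused only in the primary test.
- A reader might infer that the test cannot see a difference in pattern at all. That holds only for paths that meet at month 6, and nothing in the article predicts such a course for CRP.
- A reader might say the article labels the CRP mixed model exploratory. The word occurs in the paragraph on secondary measures. It reaches CRP because that paragraph says it follows the methods for the primary measure, so this is an inference, though a natural one.
- A reader might conclude that a joint test of the monthly profile should replace the ANCOVA. The table shows a trade-off. At AR(1) 0.8 the joint test loses about 28 points under linear divergence (45% against 72%). Gains of about 1.49 times in information for linear divergence under compound symmetry belong to the 1-df trend test, which does not detect a transient difference. No single test offers both advantages.

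On missing data, the article expects few gaps and plans sensitivity analyses if data are not missing at random. This limits the loss, but it does not give a woman without a month-6 value a place in the primary test.

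**Conclusion.** The point holds as a mismatch of scope. The primary CRP test answers whether the diets differ at month 6 given baseline, while the primary aim asks about the pattern of change. The analysis that addresses pattern is not fixed in advance. The mismatch matters most for how a null result is read: with a difference that closes by month 6, the test rejects 5% of the time whatever happened earlier. With 0.3 SD still present at month 6 it has 72-95% power, so it is not a weak test of its own question.

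The power figures rest on the assumed SD scale, correlations and 135 women per arm. The 2-8% variance reduction also assumes that 10% miss month 6, have months 1-5, and are missing at random. The mismatch itself needs none of these assumptions. The change is worth making, though the existing test remains valid for a 6-month difference.

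**What to change.** - Word the primary hypothesis as a baseline-adjusted difference in CRP between the two diets at 6 months, and state that a null result there does not show equal patterns of change.
- Prespecify the planned mixed model for CRP in the two diet arms: months 1-6 as response, baseline CRP, month as a factor, diet and diet-by-month. A baseline-by-month term lets the baseline slope differ by month, as the month-6 ANCOVA does implicitly. Take its month-6 diet contrast as the primary test and estimate, and keep the two-point ANCOVA as a check.
- Name one diet-by-time contrast from the same model, for example the 1-df linear trend, as the key test of pattern. Choose it for the shape expected, since a linear trend will miss a transient difference, and report all monthly estimates with intervals.
- Fix this model before any plot by diet is seen. Leave linear, nonlinear and piecewise curves as exploratory.
- Do not make the 6-df joint test primary.

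The cost is revised wording and slightly more modelling, with no new samples or visits. The return in month-6 precision is modest. What is gained is that women without a month-6 value stay in the primary analysis and the aim, hypothesis and test agree.

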#### Secondary Aims

1) To explore whether circulating factors associated with glucose homeostasis, chronic inflammation, and cellular oxidation display similar patterns of change in response to progressive fat loss as circulating hormones associated with sex steroid metabolism.

2) To determine whether either dietary pattern has a differential effect on the magnitude or rate of fat loss and lean tissue changes using a number of devices that permit ongoing and accurate measurements of body composition.

### Patient Recruitment (Study Setting and Participants)

CHOICE recruits women who have been treated for breast cancer and attend Rocky Mountain Cancer Centers in Denver, CO, USA. There are approximately 2000 women enrolled in the clinic. Clinic physicians refer breast cancer survivors who meet the eligibility criteria. Participants are also recruited by way of study flyers and brochures posted throughout the clinical facility. Written informed consent is given by subjects when they choose to participate in the program. Following informed consent, participants complete questionnaires that provide demographic, lifestyle and clinical data including age, marital status, ethnicity, level of education, household income, medical history, medicine and supplement use, PAR-Q (Physical Activity Readiness Questionnaire), and emotional well-being. Participants are also interviewed regarding their dieting, weight history and readiness for engaging in a comprehensive weight loss program. This population has a mean age of 60; they are > 98% white and over 50% have post baccalaureate training. While not representative of the general population, this population has proven a very high compliance rate in previous diet-cancer studies conducted by our laboratory [57,65,66].

### Eligibility

Participants must be referred by their clinical oncologist, have a pathology report confirming the resected stage of breast cancer and documentation of the type of systemic adjuvant therapy, as well as have a BMI in the overweight or obese class I range (BMI 25-34.9 kg/m^2^). Eligible participants: must be at least 4 months post radiation or chemotherapy treatment for breast cancer with no evidence of metastatic disease; must not anticipate having surgery over the study duration period; must not follow a special diet excluding foods or food groups; have not lost 2 or more kg of body weight over the month preceding study initiation; must not be taking pharmaceuticals or supplements for weight management; are not being treated for diabetes or blood glucose control; have no history of eating disorders; do not have digestive issues that may interfere with dietary intake, such as irritable bowel syndrome, Crohn's disease, or diverticulitis; have never had surgery involving constriction or removal of any portion of the gastrointestinal tract; have not been diagnosed with hepatitis B, C, or HIV; do not have implanted electronic devices such as a pacemaker; and do not use tobacco products. Participants must also be willing to follow a dietary plan prescribed for the duration of the study; adhere to American Cancer Society alcohol guidelines (≤ 1 standard drink per day); maintain or increase physical activity as prescribed to achieve negative energy balance required for 0.5-1.0 kg weight loss per week; wear a pedometer and record daily activity; wear an accelerometer/heart rate monitor for 2 weeks during the study (1 week at the beginning and 1 week at the end of the study); wear a body or swim suit and cap for body composition testing; record food intake daily; and attend up to ten one-on-one clinic visits and 5 group visits with seven fasting blood and first-void urine samples in the intervention groups, or three one-on-one clinic visits and two fasting blood and first-void urine samples in the control group over 26 weeks.

### Study Groups

#### Control

Individuals accrued to the non-intervention control group are given the same information currently provided to all breast cancer patients about the importance of avoiding post treatment weight gain, and the health benefits of having a BMI in the normal range. Clinical specimens, questionnaire data, body composition, energy expenditure from activity and anthropometric data are collected at the baseline and 6-month (end of study) visits.

